## Abstract

**Background:**

Targeting modifiable lifestyle factors including diet and physical activity represents a potentially cost-effective strategy that could support a growing population of colorectal cancer survivors and improve their health outcomes. Currently, effective, evidence-based interventions and resources helping people after bowel cancer to adopt new lifestyle habits are lacking. The aim of this trial is to test the Healthy Eating and Active Lifestyle After Bowel Cancer (HEAL-ABC) intervention to inform a future definitive randomised controlled trial.

**Methods/design:**

This is a feasibility randomised controlled trial. A total of 72 survivors who have completed surgery and all anticancer treatments will be recruited. The intervention group will receive HEAL-ABC resources based on behaviour change theory combined with supportive telephone calls informed by motivational interviewing every 2 weeks during the 3-month intervention, and once a month for 6 months to follow-up. Participants in the control group will follow usual care and have access to resources available in the public domain. The study is testing feasibility of the intervention including adherence and ability to collect data on anthropometry, body composition, diet, physical activity, behaviour change, quality of life, blood markers, contact with healthcare services, morbidities and overall survival.

**Discussion:**

The proposed study will add to the evidence base by addressing an area where there is a paucity of data. This study on lifestyle interventions for people after colorectal cancer follows the Medical Research Council guidance on evaluating complex interventions in clinical practice. It focuses on people living after treatment for colorectal cancer and targets an important research area identified by cancer survivors as a research priority reported by the National Cancer Institute and James Lind Alliance UK.

**Trial registration:**

ClinicalTrials.gov NCT04227353 approved on the 13th of January 2020

**Supplementary Information:**

The online version contains supplementary material available at 10.1186/s40814-020-00721-y.

## Background

Over recent decades, the number of people living with and beyond cancer has continued to rise worldwide. Current survival rates are associated with increased cancer incidence reaching 18 million new cases in 2018 [1], ageing of the population [2] and advances in early cancer detection and treatment [3]. Several definitions of cancer survivorship have been proposed. One approach in research and within the medical community defines a person who has survived cancer as “living with and beyond cancer” [4].

There is mounting evidence that links lifestyle choices regarding diet and physical activity to primary cancer risk [5]. Likewise, large cohort studies have shown that people who have survived cancer and followed healthy eating and active lifestyles can improve their survival rate [6]. It is therefore hypothesised that adherence to healthy diet and physical activity in people who have completed cancer treatment may reduce cancer risk, recurrences, comorbidities, new cancers, cardiovascular diseases and diabetes and improve overall survival rates [7]. However, there is insufficient evidence from randomised controlled trials (RCTs) to support this hypothesis. This has been highlighted in a systematic review on dietary interventions in adult cancer survivors, which revealed an uneven distribution of research across cancer sites [8].

Currently, evidence in cancer survivorship is centred predominantly on breast cancer studies [8, 9]. There is a paucity of evidence for colorectal, gynaecological and prostate cancer. The global burden of colorectal cancer (CRC) is expected to increase by 60%, which is more than 2.2 million new cases, by 2030 [10]. In England and Wales, almost six out of every ten people diagnosed with CRC survive their disease for 10 years or more [11]. However, survival is often affected by a number of physical and psychological problems including comorbidities [12], side effects from treatment including neuropathy, bowel disturbances [13], weight changes [14], cancer recurrences [15] or new cancer diagnosis [16] and surgical procedures can leave a proportion of patients with stoma. All these factors have a substantial impact on survivors’ quality of life [17, 18]. Helping people after cancer to follow a healthier lifestyle is a low-cost strategy that has the potential to mitigate health complications people may face after their treatment. To date, evidence indicates limited success at initiating long-term lifestyle changes in people living after cancer [8, 19] and effective evidence-based approaches to help people make substantial lifestyle changes after CRC are lacking.

Difficulties in identifying an effective lifestyle intervention may be influenced by the variety of interventions that have been tested and also by limitations in resources allocated to the development of an appropriate intervention. Dietary interventions are complex; however, there is guidance available from the UK Medical Research Council (MRC) on the development and evaluation of complex interventions in healthcare [20]. This guidance suggests piloting and feasibility testing to enhance the development and integration of complex interventions into healthcare. It also suggests involvement of participants in intervention development and conducting qualitative work to test acceptability, barriers and facilitators to adherence and uptake. There are diet and lifestyle interventions that have been developed incorporating some of these points to a high standard for people after breast cancer [21–23]; however, high-quality interventions for people after CRC are currently absent.

The proposed study aims to build on the current knowledge base by following MRC Guidance [20]. Prior to the protocol development, people after CRC were asked about their views and experiences of eating after a cancer diagnosis and their motivation for change [18] along with their preferences regarding delivery of lifestyle information [24]. This was combined with the development of an intervention resources which involved work with CRC survivors’ and healthcare professionals [25]. Behaviour change theory was integrated throughout the resource [26].

The purpose of this study is to evaluate the feasibility of conducting a fully powered trial for a Healthy Eating and Active Lifestyle After Bowel Cancer (HEAL ABC) intervention versus usual care.

## Methods/design

This is a feasibility parallel group RCT using 1:1 randomisation*.* The study follows CONSORT guidelines for reporting a pilot or feasibility trial [27] and follows the Standard Protocol Items: Recommendations for Interventional Trials (SPIRIT) [28]. Version 6 of the protocol has been finalised on 7th of January 2020.

### Eligibility and exclusion

Participants will be included in the trial if they are over 18 years old, more than 12 weeks post-surgery and have completed all active anti-cancer treatments (surgery, radiotherapy or chemotherapy). Detailed inclusion and exclusion criteria are presented in Table 1.

**Table 1 Tab1:** Inclusion and exclusion criteria

Inclusion criteria	Exclusion criteria
Adults, age ≥ 18	Age < 18
Minimum 12 weeks post-surgery and/or active treatment	Less than 12 weeks post-surgery or active treatment
Completed all active anti-cancer treatments, including surgery, radiotherapy or chemotherapy	Receiving treatment for malignancy, secondary malignancy
No serious health complications	Short bowel syndrome, Crohn’s disease, ulcerative colitis, diverticulitis or jejunostomy, previous stroke, congested cardiac failure or oedema, hepatic or renal failure
No specific dietary requirements	On any therapeutic diets, multiple food intolerances or allergies
Body Mass Index ≥ 20 kg/m^2^	Body Mass Index < 20 kg/m^2^
Unintentional weight loss ≤ 5% in the previous 3–6 months	Unintentional weight loss >5% in the previous 3–6 months
Following < 4 of the WCRF/AICR recommendations	Already following ≥ 4 WCRF/AICR recommendations
Ability to work with computer, smart phone or tablet	Inability to work with computer, smart phone or tablet
Ability to give informed consent	Inability to give informed consent

*WCRF/AICR* World cancer Research Fund and American Institute of Cancer Research

### Recruitment and consent

Participants will be recruited from outpatient CRC surveillance clinics in Great Manchester (Fig. 1). In the hospitals, appropriate participants will be identified from clinical records and screened by clinic staff. A record of people approached and individuals that express an interest will be kept. A patient information sheet and researcher contact details will be provided to facilitate follow up of potentially interested participants. The COVID-19 pandemic in UK in 2020 may preclude using this face to face approach, in which case an alternative non-face to face method of recruitment will be adopted. Participants who are interested in taking part will be consented, randomised and allocated to one of two trial arms. Baseline data will be collected following randomisation to the control or intervention arms.

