### Baseline assessment

At baseline, details of patients’ characteristics will be collected using a sociodemographic questionnaire (see Additional file 1). Patient medical records will be used to collect information on cancer staging using the Classification of Malignant Tumours (TNM classification) post-surgery [35], type of chemotherapy/radiotherapy, disease site and operation details.

Further baseline measurements will include anthropometry, body composition, dietary intake, physical activity, quality of life, behaviour change assessment and blood tests.

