### Randomisation

Participants will be randomised into control and intervention groups using the sealedenvelope.com [57] block randomisation. The randomisation will be stratified for hospital site and cancer site (colon or rectum). An independent person outside of the research team will generate the allocation sequence and assign participants into their groups. Participants cannot be completely blinded to the intervention but effort was taken to blind differences between HEAL and HEALTH group for participants through the provision of written materials and following the same assessment. The researcher will not be blinded to the intervention and outcomes.

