### Statistical analysis

Quantitative data will be analysed using descriptive statistics displayed with 95% confidence intervals. Changes in outcomes between the intervention arm and control, estimate parameters using means and standard deviations will be descriptively compared and will inform a sample size calculation for a full RCT. All quantitative data will be analysed in STATA 15 (StataCorp, TX: StataCorp LLC) [58].

Qualitative interview transcripts will be managed using NVivo 12 software (QSR International Pty Ltd., Doncaster, VIC, Australia) and analysed using the five stages of framework analysis [59]: familiarisation, developing a thematic framework, indexing, charting and mapping and interpretation. During the first stage (familiarisation) the researcher will become immersed in the data, by reading and re-reading the transcripts. Next, a thematic framework will be developed. After this, transcripts will be indexed (coded) line by line using the thematic framework but remaining open to new themes that emerge. Next, the data will be entered into a chart, so that coded extracts can be attributed to individual participants. Finally, participants’ views will be compared and contrasted, and the data presented schematically (mapping). Contrasting explanations will be explored.

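### Baseline is measured after allocation, so self-reported and behaviour-reactive baselines can be influenced by arm and can bias the changes and effect sizes carried into the full trial

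*Protocol article*

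**What the plan says.** The Recruitment and consent section sets the order in two consecutive sentences: "Participants who are interested in taking part will be consented, randomised and allocated to one of two trial arms", and then "Baseline data will be collected following randomisation to the control or intervention arms". Table 4 ticks allocation and the baseline measures in the same Baseline column. It is compatible with that order but does not itself say which comes first.

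On masking, the Randomisation section says "The researcher will not be blinded to the intervention and outcomes". Of participants it says "Participants cannot be completely blinded to the intervention but effort was taken to blind differences between HEAL and HEALTH group for participants".

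The Baseline assessment section lists what is then measured: "Further baseline measurements will include anthropometry, body composition, dietary intake, physical activity, quality of life, behaviour change assessment and blood tests". Its subsections specify a 3-day food diary entered in INTAKE24, the GPAQ, a week of pedometer wear, the SF-12 and a HAPA-based questionnaire.

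On use of the data, the Statistical analysis section says "Changes in outcomes between the intervention arm and control, estimate parameters using means and standard deviations will be descriptively compared" and that this will inform the sample size of a full RCT. The Outcomes section likewise lists effect sizes for diet, physical activity and behaviour change among the things to be determined.

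**The concern.** Randomisation makes the arms comparable on what is measured before it. A baseline taken afterwards is protected only if knowledge of the arm cannot alter it.

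That is doubtful for several measures here. A person who has just been assigned to a diet and activity programme may eat, walk or report differently over the next few days. So may a person who has been pointed to public websites. The unblinded researcher also instructs participants on completing the diary. The Study limitations section itself acknowledges a heavy dependence on recall and accurate reporting.

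Two things follow. First, a shift in one arm's baseline passes directly into that arm's change score. Second, people who withdraw on learning their arm, before any measurement, supply no baseline. They drop out of every change analysis and cannot be described on these measures.

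At stake are the between-arm changes and effect sizes for diet, activity, motivation and quality of life that the trial is meant to pass on to its successor.

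**Working it through.** **The article's own figure.** The only sample-size figure is 72 recruited for 60 completers with up to 15% dropout. Per arm, 30 / 0.85 = 35.3, rounded up to 36, and 2 × 36 = 72. It reproduces. The point does not depend on it, but it supplies n = 30 completers per arm for the precision figures below.

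**Which measures are exposed.**

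| Measure | Source in the article | Open to influence by allocation at baseline? |
|---|---|---|
| Food diary / INTAKE24 | Self-report | Yes |
| GPAQ, SF-12, HAPA | Self-report | Yes |
| Pedometer, one week | Worn by participant | Yes, through behaviour |
| Weight, bio-impedance | Instrument, standard operating procedures | Little |
| CT body composition | Existing scan nearest the assessment | Little |
| Blood markers | Routine results from records | Little |

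**Bias formulas.** Let allocation move the baseline mean of one arm by b (in SD units) and leave follow-up values alone. Let rho be the baseline to follow-up correlation.

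- Difference in change: off by b in absolute value.
- Baseline-adjusted difference: off by about rho × b.
- Difference in follow-up values: off by 0.

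The sign depends on which arm moves and in which direction. The article gives no information on either.

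**Assumed inputs (none is in the article):** b = 0.1 to 0.3, rho = 0.3 to 0.7, SD 1 at both times.

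- Change contrast: bias 0.1 to 0.3 SD.
- Adjusted contrast: from 0.3 × 0.1 = 0.03 SD to 0.7 × 0.3 = 0.21 SD.

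**Set against precision.** With 30 per arm, the 95% half-width for the difference in change is 1.96 × √(2(1 − rho)) × √(2/30). For the adjusted difference, the standard error is √(1 − rho²) × √(2/30). Coverage of a nominal 95% interval, with k = bias / standard error, is Φ(1.96 − k) − Φ(−1.96 − k).

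| rho | Half-width, change | Coverage, change (b = 0.1 / 0.2 / 0.3) | Coverage, adjusted (b = 0.1 / 0.2 / 0.3) |
|---|---|---|---|
| 0.3 | 0.60 | 93.8% / 90.0% / 83.4% | 94.8% / 94.3% / 93.5% |
| 0.5 | 0.51 | 93.3% / 87.9% / 78.7% | 94.4% / 92.7% / 89.7% |
| 0.7 | 0.39 | 92.1% / 83.0% / 67.7% | 93.3% / 88.2% / 79.3% |

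For the follow-up-only difference the half-width is 1.96 × √(2/30) = 0.51 SD, the same as the change score at rho = 0.5, with no bias from this source.

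**Effect on planning.** With n per arm = 2(1.960 + 1.282)² / d² = 21.02 / d² (two-sided 5%, 90% power), an assumed true effect of 0.5 SD needs 85. Misread by 0.2 SD, it would give 234 (at 0.3 SD) or 43 (at 0.7 SD).

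**The case against.** The strongest reply is that this is a feasibility trial with descriptive comparisons and no hypothesis test. Recruitment, retention, data completion, goals set and qualitative acceptability need no unbiased baseline contrast. A uniform shift moves means but not SDs, so the SD estimates for the next sample size would survive. With 30 per arm, the assumed bias lies inside the interval's half-width. All of that stands, and it limits the consequence to the changes and effect sizes. It does not remove the point, because the article names those as outputs to be carried forward.

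The article also reports an effort to mask the difference between the two groups, so it would be too strong to say that participants simply know their arm. Masking is stated to be incomplete, which is enough for the concern.

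It would likewise be wrong to say that every change contrast is exposed, given the record-based and instrument measures. It would also be wrong to say that no analysis helps, since a follow-up comparison avoids this bias.

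A reader might further infer that eligibility is checked with measures taken after randomisation, because two criteria, "Following < 4 of the WCRF/AICR recommendations" and "Body Mass Index ≥ 20 kg/m^2", concern diet, activity and body size. The documents do not support that. Table 4 ticks the eligibility screen only before baseline, and the recruitment section has clinic staff screen from clinical records. The article does not say how the lifestyle criterion is established, but a condensed article may leave that to the full protocol.

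Finally, leavers before baseline are already counted as losses, because retention is completers divided by randomised. What they lack is a baseline value.

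**Conclusion.** The point holds for the self-reported and behaviour-reactive outcomes: diet, GPAQ, pedometer steps, HAPA and SF-12. The article fixes an order, randomise and then measure, that leaves these baselines open to influence by allocation. It then uses changes from them to inform the full trial.

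The size cannot be known from the document. Under the assumed ranges the change contrast is biased by 0.1 to 0.3 SD and an adjusted contrast by 0.03 to 0.21 SD. Coverage of a nominal 95% interval for the change contrast then lies between 93.8% and 67.7%. These figures rest on a uniform shift in one arm, equal SDs at both times, 30 completers per arm and a normal approximation. They illustrate the mechanism and do not predict what will happen. The feasibility outcomes, the record-based and instrument measures, and the eligibility screen are not called into question.

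**What to change.** In the Recruitment and consent section, and in Table 4, put the steps in this order: consent, all baseline measures including the diary and the pedometer week, then randomisation and release of the allocation by the independent person. In Table 4, place allocation after the baseline measures instead of in the same column. Report the number consented but not randomised. The sample size of 72 need not change, and bias from this source is removed by design.

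The cost is about a week's delay to allocation, mainly for the pedometer week, possibly one more contact with each participant, and a few consented people who are never randomised. That last count is itself useful feasibility information.

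If the order cannot be changed, report between-arm differences in follow-up values alongside the changes for the exposed outcomes, and state the limitation. This repairs less: it does not recover baselines for people who leave before measurement.

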**Fig. 1 Fig1:**
[figure not shown]
Study flow diagram

### Intervention

The intervention group will follow the HEAL ABC programme involving a written resource (Fig. 2) combined with supportive telephone calls every 2 weeks during the intervention and once a month during the follow-up period.

**Fig. 2 Fig2:**
[figure not shown]
Healthy Eating and Active Lifestyle After Bowel Cancer—HEAL ABC resources

### HEAL ABC resources

Participants allocated to the intervention will be encouraged to follow HEAL ABC resources (Fig. 3) in order to make a healthy eating and active lifestyle changes. Development of the HEAL ABC resources and qualitative evaluation from people after bowel cancer, healthcare professionals and researchers is described elsewhere [25].

**Fig. 3 Fig3:**
[figure not shown]
Healthy Eating and Active Lifestyle After Bowel Cancer—HEAL ABC structure [25]

Resources are based on the World Cancer Research Fund and American Institute of Cancer Research (WCRF/AICR) guidelines on diet and physical activity for cancer prevention [7, 29]. Suggestions for physical activity and exercise are based on a strategy, which integrates physical activity into everyday life tasks, that has been shown to be more effective than structured exercise programmes in exercise facilities [30, 31]. Resources have incorporated recommendations from the Health Action Process Approach (HAPA) [26], a behaviour change theory.

### Behaviour change

The HEAL ABC resources consist of 12 booklets and additional supportive sheets. The order of the booklets is not specified. Participants start with an assessment booklet and review their current diet and physical activity level. Following the assessment, participants will be assigned their first booklet based on the one they perceive to be the easiest for setting an incremental goal and achieving it [32]. Meaning participants start with the booklet of the highest self-efficacy and after they achieve a successful behaviour change, they can move more confidently to the next booklet. During the follow-up period, participants will use the follow up booklet, which helps them to continue with changes they have made and encourage them to set new goals (Table 2).

**Table 2 Tab2:** Content, strategies and behavioural targets of the Healthy Eating and Active Lifestyle After Bowel Cancer programme

Target	Task	Source
Increase awareness of the need to change	Assessment of body, diet and physical activity	Assessment booklet
Understanding benefits of healthy eating habits and activity lifestyle	Information about healthy recommendations	All booklets
Learning about new skills on healthy eating and active lifestyle	Learning about healthy options, cooking and shopping tips, understanding portion sizes, choosing healthier alternatives/adding activities to daily routines	All diet-related booklets/physical activity booklet
Exploring current habits and identifying where the change can be made	Targeted questions on specific dietary habits/physical activity	All diet-related booklets/physical activity booklet
Selections of specific goal(s)	Action plan	All booklets
Creating detailed plan how to achieve selected goal	Action plan	All booklets
Understanding own motivation, risks, barriers, coping strategies and readiness to change	Get ready for your action section	All booklets
Calendar with notes to record	Make your notes section	All booklets
Review of the goal and action	Review plan	All booklets
Instruction to start new booklet, follow-up with participants progress, encouragement and support	Supportive calls every 2 weeks during intervention and once a month during follow up	Telephone calls
Maintenance of new behaviour, encouragement to start new changes	Calendar for 12 weeks to track progress and continue with changes, opportunity to plan and track new goals	My journey to better health booklet

The HAPA model for behaviour change was selected for the resources as it has been developed directly to target health-related behaviours [26]. This theory takes into consideration behavioural aspects that support the formation of intention to change to post-intentional phase of behaviour maintenance and recovery. The HAPA constructs have been mapped in HEAL ABC booklets, incorporated into tasks and activities within the booklets to support intention, action, maintenance and the recovery self-efficacy of study participants (Table 3).

**Table 3 Tab3:** Health Action Process Approach (HAPA) constructs mapped within the Healthy Eating and Active Lifestyle After Bowel programme

Construct	Implementation in HEAL ABC programme	Construct's description
Action self-efficacy	Get ready page in the booklet—how confident are you about making this change?	Participants believe in their own ability to improve their diet and to become more active.
Outcome expectancies	Get ready page in the booklet—why do you want to make this change?	Participants believe they will benefit from changing their behaviour and achieve positive outcomes when taking part in the HEAL ABC programme.
Risk perception	Get ready page in the booklet—why do you want to make this change?	Participants believe there will be negative consequences if they do not change their dietary habits and activity level.
Action planning	Action plan page in the booklet—creating a specific action plan	Participants are supported to identify opportunities to incorporate new eating habit(s) and activity(s) into their everyday lives.
Coping planning	Get ready page in the booklet—if things do not go as you plan, what steps will you take to make sure you stick to your plan?	Participants are supported to identify barriers and make plans to address them.
Coping self-efficacy	Motivational interviewing during the phone calls	Participants believe in their capacity to continue with a new behaviour even when barriers arise.
Recovery self-efficacy	Motivational interviewing during the phone calls	Participants believe they can return to their new behaviour even when they disengaged with their new activities for a long period.

